## Data collection and management

### Plans for assessment and collection of outcomes {18a}

#### Screening visit

Screening and inclusion of patients will be performed not earlier than 3 days and not later than one day before the planned surgical procedure, to ensure the patient has enough time to consider the decision to participate in the study. All screened patients are documented in a screening log. If patients do not wish to participate in the study, the reasons will be documented accordingly. If patients fit inclusion/exclusion criteria and agree to participate, they will need to give written informed consent, after adequate time for consideration. Therefore, at the screening visit, a detailed description of the study and further instructions are discussed with the patient, including methods of abdominal and wound irrigation, risk-benefit ratio, and follow-up schedule.

#### Visit 1 (inclusion)

After the investigator has reviewed the inclusion and exclusion criteria again and having received written consent by a patient, demographical data and medical history (incl. age, gender, body height, body weight, BMI, ASA, concurrent medication with effects on wound healing, history of SSI, history of radio/chemotherapy, diabetes, smoking, alcohol consumption, duration of pre-operative hospital stay) and the diagnosis will be documented. In addition, the Charlson Comorbidity Index (CCI) will be calculated, which is a prognostic score that is used in many recent trials to simplify the comparability and evaluation of multimorbid study populations [29]. In addition, the investigator will perform a physical exam of the planned abdominal incision area.

#### Visit 2 (surgery/randomization)

Documented parameters of the surgical procedure include the urgency (emergency/elective), type of surgical procedure (colorectal and/or small bowel and/or hepato-biliary and/or pancreatic and/or splenectomy and/or gastric and/or oesophageal and/or others) the duration of surgery (incision until complete skin closure), the LOC according to CDC classification (LOC II–IV; see Table 2), the type and timing of perioperative antibiotic prophylaxis, the intraoperative use of wound edge protectors, and the prophylactic changing of gloves during of the operation. The type (transverse/midline) and length (cm) of the incision, as well as the creation or presence of an enterostomy (yes/no), the abdominal wall and wound closure technique (subcutaneous sutures, stapler/suture, continuous/single) and used suture material, the placement and type of intraabdominal drains will also be recorded. If the operating surgeon decides that incomplete closure of the wound and/or any other wound-related procedure after the study intervention (e.g. negative pressure treatment) is necessary for the benefit of the patient, the patient will have to be excluded from the study. Furthermore, if prophylactic or therapeutic postoperative intraabdominal irrigation is performed via an irrigation-suction-drain system, the patient must be excluded from the study.

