### Criteria for discontinuing or modifying allocated interventions {11b}

Participants of the study can withdraw their consent to take part at any time without declaration of reasons. All hitherto collected data are subject to analysis, within the consent of the participant. The principal investigator may exclude patients from the study, if patients’ safety is at risk or if there is insufficient compliance of the patient. In order to generate a meaningful database, excluded patients can be replaced by recruitment of new patients. If a patient does not receive NaOCl/HOCl or Ringer solution irrigation of the peritoneal cavity or wound, this does not automatically lead to exclusion of the study.

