### Relevant concomitant care permitted or prohibited during the trial {11d}

No additional treatments or interventions will be performed within the study. All patients will receive standard perioperative antibiotic prophylaxis, the timing and type of which will be recorded in the eCRF. Furthermore, the application of abdominal wall protectors is recommended for contaminated procedures and must be recorded in the eCRF. A change of gloves ahead of wound closure is frequently performed in contaminated procedures and must also be recorded in the eCRF. If an irrigation-suction-drain is placed in the abdominal cavity and the patient receives prophylactic intraabdominal irrigation therapy via this device postoperatively, the patient must be excluded from the study. If indicated for medical reasons, all kind of medication is permitted during the study. Postoperative medication with known adverse effects on wound healing (e.g. antibiotics, corticoids, and other immunosuppressive agents) will be recorded in the eCRF. Any operative or interventional revision of the wound will be documented as AE/ SAE in the eCRF.

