**Fig. 1 Fig1:**
[figure not shown]
PAISI intervention flow scheme (according to SPIRIT statement 2013 [28])

**Table 3 Tab3:** PAISI study visits (according to SPIRIT statement 2013 [28])

	Study period				
	Inclu.	Rand.	Post-allocation		Close-out
Study visit Number	1	2	3	4	5
Timepoint	− 1–3 days	day 0)	day 5	day 10 (+5)	day 30 (+5)
Informed consent	X				
Inclusion and exclusion criteria	X				
Randomization		X			
Intervention (IPI with 1500ml NaOCl/HOCl solution)		X			
Control (IPI with 1500ml Ringer solution)		X			
Demographical data	X				
Medical history and Charlson Comorbidity Index	X				
Medication with known effects on wound healing	X				
Physical examination	X				
Type of operation		X			
Duration of operation		X			
Level of contamination		X			
Type and length of incision		X			
Abdominal wall closure technique and suture material		X			
Presence of an enterostomy		X			
Use of wound edge protectors		X			
Changing of gloves		X			
Placement and type of-intra-abd. drains		X			
Postoperative medication with known effects on wound healing			X	X	X
Documentation of SSI			X	X	X
Documentation of other postoperative complications (Clavien Dindo and CCI)			X	X	X
Documentation of re-operation			X	X	X
Documentation of postoperative intra-abd. irrigation via irrigation-suction drainage system			X	X	X
Documentation of AE/SAE of special interest		X	X	X	X
Duration of hospital stay					X

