## Statistical methods

### Statistical methods for primary and secondary outcomes {20a}

The intention-to-treat (ITT) set consists of all patients who received irrigation of the abdominal cavity before closure of the abdominal fascia with one of the study solutions. Analysis will be performed as randomized regardless of the actual intervention and regardless of any further medical or surgical treatments. The Per-Protocol (PP) set consists of patients treated according to protocol, excluding any major protocol violations. The PP set will be analysed as treated. The Safety (SA) set will consist of all patients in the ITT set, analysed as treated.

All primary and secondary analyses will be performed on the ITT set. Sensitivity analysis of the primary endpoint will be performed on the PP set. The SA set will be used for the safety analyses. The incidence of SSI within 30 days after surgery will be compared between the two study groups using the one-sided group sequential test of two proportions at the 2.5% significance level with a total of two looks at the data. The primary endpoint analysis will be performed on the ITT set. Since the ITT set includes all patients who were treated in the study regardless of any further medical or surgical treatments, it is expected, that the SSI rates 30 days post-surgery will be available for most patients. Nevertheless, it is possible that some patients do not reach the primary endpoint due to death, withdrawal of informed consent, loss to follow-up, or other unforeseen reasons. Patients who die before day 30 will be considered as having SSI at time of death regardless of the intervention group, unless SSI was documented earlier. All other missing primary endpoint data will be dealt with using multiple imputations based on binary logistic regression models including LOC, ASA, BMI, age, diabetes, type of surgery, duration of surgery, use of wound-edge protectors, and intraoperative changing of gloves.

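### Post-randomisation exclusion and replacement for wound procedures or drain irrigation contradict the intention-to-treat rule and could lose primary-endpoint cases

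*Protocol article*

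**What the plan says.** Sections {11a} and {16a} place randomisation at the end of surgery, before fascia closure. Everything below therefore happens after allocation.

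- **Visit 2 (surgery/randomization), wound:** the patient is to be excluded if the operating surgeon decides that incomplete closure or "any other wound-related procedure after the study intervention (e.g. negative pressure treatment) is necessary for the benefit of the patient".
- **Visit 2, irrigation:** "if prophylactic or therapeutic postoperative intraabdominal irrigation is performed via an irrigation-suction-drain system, the patient must be excluded from the study".
- **Concomitant care {11d}:** the irrigation rule again, but narrower. If an irrigation-suction drain is placed and "the patient receives prophylactic intraabdominal irrigation therapy via this device postoperatively, the patient must be excluded from the study". Therapeutic irrigation is not named.
- **Discontinuation {11b}:** "In order to generate a meaningful database, excluded patients can be replaced by recruitment of new patients".
- **Statistical methods {20a}:** the ITT set is everyone whose abdominal cavity was irrigated with a study solution. "Analysis will be performed as randomized regardless of the actual intervention and regardless of any further medical or surgical treatments". All primary and secondary analyses use this set; major protocol violations are removed from the PP set only.
- **Table 3:** "Documentation of postoperative intra-abd. irrigation via irrigation-suction drainage system" is collected at the visits on days 5, 10 and 30.
- **Blinding {17a}:** the surgical team cannot be blinded, because of the smell of the solution.

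**The concern.** For an irrigated patient who later meets one of the triggers, one section orders exclusion from the study and another keeps the patient in the primary analysis. Staff and statistician could each follow the protocol and reach different datasets.

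Two mechanisms are at stake, and they should be kept apart.

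1. **Irrigation through a drain.** The primary endpoint includes organ/space infection. Therapeutic irrigation may be a response to such an infection, and it is recorded up to day 30. If so, the exclusion depends on the outcome.
2. **Wound decisions in the operating room.** No SSI can have occurred yet, but the decision is taken after allocation by a surgeon who knows the arm. Exclusion could therefore differ between arms.

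Equal loss of cases lowers both rates and costs power. Unequal loss biases the comparison in either direction: loss from the experimental arm creates an apparent benefit, and loss from the control arm hides a real one. Replacement restores the headcount but not the comparability of the arms.

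**Working it through.** **1. The rules applied to one patient.** Take a patient who was randomised and irrigated, and who receives therapeutic irrigation through a drain on day 8.

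| Section | Consequence |
|---|---|
| Visit 2 | excluded from the study |
| {11d} | not excluded (only prophylactic irrigation is named) |
| {11b} | if excluded, may be replaced |
| {20a} | in the ITT set, analysed as randomised |

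If exclusion merely ends follow-up, an SSI not yet documented becomes missing and is multiply imputed. The listed covariates are LOC, ASA, BMI, age, diabetes, type and duration of surgery, wound-edge protectors and glove change. Postoperative irrigation and wound treatment are not among them, so a likely case would be imputed like a patient without the event.

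**2. The plan's own figure.** Inputs from {14}: 4% vs 16%, one-sided 2.5%, 80% power, bounds 2.963 and 1.969, interim futility bound 0.555, continuity correction.

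- Fixed design, unpooled variance: n = (1.960 + 0.842)² × (0.04×0.96 + 0.16×0.84) / 0.12² = 94.19 per arm.
- Inflation implied by the stated bounds, 1.0556: 94.19 × 1.0556 = 99.42.
- Continuity correction: (99.42/4) × [1 + √(1 + 4/(99.42×0.12))]² = 115.49, so 116 per arm and 232 in total.
- Drop-out: 232/0.80 = 290.

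The sample size reproduces and is not in dispute.

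**3. How many cases are exposed.** Section {6a} reports an in-house SSI rate of 13%, of which 7% were class III. This can mean 7 of 13 percentage points (share s = 7/13 = 54%) or 7% of SSIs (s = 7%). Expected SSIs at 116 per arm are 0.16×116 = 18.6 (control) and 0.04×116 = 4.6 (experimental). Class III cases are then about 10.0 and 2.5 (s = 54%), or about 1.3 and 0.3 (s = 7%).

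**4. Equal exclusion, with replacement to 116 per arm.** Let f be the share of class III cases excluded. The documents do not give f; 25% and 50% are assumptions. With g = s×f, the observed rate is p′ = p(1 − g)/(1 − p·g). Example with s = 54% and f = 25%: g = 0.1346; control 0.16×0.8654/(1 − 0.0215) = 14.2%; experimental 0.04×0.8654/(1 − 0.0054) = 3.5%.

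Power is from simulation of the two-look design (58, then 116 per arm; pooled z with continuity correction; stated efficacy bounds; stopping at the futility bound).

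| s | f | control vs experimental | power |
|---|---|---|---|
| – | 0 | 16.0% vs 4.0% | 81% |
| 54% | 25% | 14.2% vs 3.5% | 75% |
| 54% | 50% | 12.2% vs 3.0% | 67% |
| 7% | 25% | 15.8% vs 3.9% | 80% |
| 7% | 50% | 15.5% vs 3.9% | 79% |

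**5. Unequal exclusion under no effect.** Both true rates are 16%, and 25% of class III cases are excluded in the experimental arm only (also an assumption). Same two looks, with the non-binding futility bound ignored.

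| s | observed rates | one-sided error, no continuity correction | with correction |
|---|---|---|---|
| no exclusion | 16.0% vs 16.0% | 2.5% | 1.6% |
| 54% | 16.0% vs 14.2% | 5.9% | 3.9% |
| 7% | 16.0% vs 15.8% | 2.8% | 1.8% |

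**The case against.** The strongest reply is that {20a} already settles the matter: the ITT set depends only on having been irrigated, and violations leave the PP set alone. Section {19} requires the eCRF also for patients who do not complete the study, with the reason for any exclusion recorded. An SSI documented before or at exclusion could therefore still count. A reader might infer that the plan deletes SSI cases from the primary analysis; the text does not say so, and that is only one reading. What stands is that Visit 2 orders exclusion from the study without limiting it to the PP set, and that no section says follow-up continues afterwards.

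A reader might also infer that therapeutic irrigation identifies an organ/space SSI. The documents do not establish this. Section {6a} lists relaparotomy, intensive care, drainage and antibiotics as treatment of class III SSI, not irrigation. LOC IV patients are eligible, so therapeutic irrigation could start at the index operation for an existing infection. Recording to day 30 fits either account. The link is plausible but inferred.

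Nor do the documents support the view that unblinded staff decide outcome-dependent exclusions. The unblinded surgeon decides on the wound at surgery; who orders later irrigation is not stated.

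The replacement sentence in {11b} follows exclusions for safety or poor compliance and may have been meant for those alone. Its wording is nevertheless general, and Visit 2 uses the same term.

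Finally, the in-house series covers elective LOC II–III surgery, whereas the trial adds emergency and LOC IV cases. The class III share is uncertain beyond the two readings of the sentence.

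**Conclusion.** The point holds as a contradiction in the current text. Visit 2, {11d}, {11b} and {20a} give incompatible instructions for patients who are already randomised and irrigated. This is a conflict between stated rules, not detail left to an analysis plan. Reading exclusion as the end of follow-up does not remove the problem, because undocumented outcomes would then be imputed without the event that prompted the exclusion.

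The size of the effect is unknown. It depends on how often these exclusions occur, how far therapeutic irrigation tracks organ/space SSI, and the class III share. Under the assumptions above, power lies between about 67% and 80% instead of 81%. With one-arm exclusion under no effect, one-sided error lies between about 2.8% and 5.9% without continuity correction (starting from 2.5%), or between 1.8% and 3.9% with it (starting from 1.6%). If such exclusions are rare, the effect is close to nil. The case for correction rests on the conflicting rules and the low cost of resolving them, not on a demonstrated bias.

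**What to change.** Reconcile {11b}, {11d}, Visit 2 and {20a} by amendment, so that:

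- incomplete closure, further wound procedures and postoperative drain irrigation are recorded, and follow-up for SSI continues to day 30;
- the patient stays in the ITT primary analysis as randomised;
- the event is a reason for exclusion from the PP set only, with one wording of the irrigation item in {11d} and Visit 2;
- randomised patients are not replaced, since the increase from 232 to 290 already covers drop-out.

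Leave the investigator's safety exclusion in {11b} unchanged. Add only that such patients' outcomes are still collected and analysed in the ITT set where consent allows. Whether irrigation or wound treatment is given is a clinical matter that this change does not touch.

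Recruitment began in September 2022. For patients already excluded, recover the day-30 outcome from records where consent allows.

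Cost: a short amendment and some retrospective data retrieval. No new procedures are needed, and the irrigation item is already in the visit schedule. The downside is that a few patients with mixed exposure remain in the primary analysis; the planned PP sensitivity analysis addresses that.

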#### Visit 3 to 5 (post-op days 5, 10, and 30)

Postoperatively, there will be 3 study visits where an independent, blinded outcome assessor trained in the diagnosis and classification of SSI according to CDC definition (SSI I–III, see Table 1) will examine wounds. Postoperative medication with known effects on wound healing (e.g. antibiotics, corticoids and other immunosuppressive agents) will be documented in the eCRF. Any surgical complication, including SSI, will be reported including its severity (according to the Clavien-Dindo Classification and CCI) and its consequent treatment. Furthermore, the rate of re-operations, mortality and occurrence of any AE or SAE of special interest will be documented. Additionally, the duration of the hospital stay (in days) will be documented on visit 5 (post-op day 30).

### Plans to promote participant retention and complete follow-up {18b}

To promote complete follow-up, a visit window of two additional days was implemented for visit 3, and 5 additional days for visits 4 and 5. If however, the patient is unable to attend visit 4 or 5 due to postoperative treatment in a rehabilitation facility or other medical reasons, a standardized protocol for evaluation and documentation of the wound or intraabdominal complications will be sent to and filled out by the treating physician. In the exceptional case that the patient has no possibility to be evaluated by a physician for visit 5, a telephone interview with the patient can be performed to assess the primary endpoint. However, in this case, the reasons why a physician cannot see the patient have to be declared on a designated form.

### Data management {19}

The documentation of the study data in adherence to the protocol is the responsibility of the principal investigator. Original data (source documents) remain in hospital medical record and information on the eCRF must be traceable and consistent with the original data. Original written informed consent signed by the patient is kept by the investigator and a signed copy will be given to the patient. No information in source documents about the identity of the patients will be disclosed. All data collected in this study must be entered in an eCRF using a REDCap database (Research Electronic Data Capture, Version 10.5.2, 2022, Vanderbilt University) [30, 31] which has to be completed by the investigator or authorized study personnel and signed by the investigator. This also applies for those patients who do not complete the study. If a patient is excluded from the study, the reason must be recorded on the eCRF. The investigator is responsible for ensuring the accuracy, completeness, and timeliness of all data in the eCRFs and in all required reports. After entry of all collected data and clarification of all queries, the database will be closed at the completion of the study. Data and results electronically recorded will be archived according to applicable law.

### Confidentiality {27}

The applicable local regulations of data privacy protection will be followed. The patients will be informed that any patient-related data and materials will be appropriately made pseudonymous and that these data may be used for analysis and publication purposes. Furthermore, the patients will be informed that their data may be inspected by monitors for the purpose of validation of a proper study conduct. Patients who do not provide consent for processing of their data, according to the data protection agreement included in the ICF, will not be included in the clinical study.

### Plans for collection, laboratory evaluation and storage of biological specimens for genetic or molecular analysis in this trial/future use {33}

Not applicable since no biological specimen will be taken.

## Statistical methods

### Statistical methods for primary and secondary outcomes {20a}

The intention-to-treat (ITT) set consists of all patients who received irrigation of the abdominal cavity before closure of the abdominal fascia with one of the study solutions. Analysis will be performed as randomized regardless of the actual intervention and regardless of any further medical or surgical treatments. The Per-Protocol (PP) set consists of patients treated according to protocol, excluding any major protocol violations. The PP set will be analysed as treated. The Safety (SA) set will consist of all patients in the ITT set, analysed as treated.

All primary and secondary analyses will be performed on the ITT set. Sensitivity analysis of the primary endpoint will be performed on the PP set. The SA set will be used for the safety analyses. The incidence of SSI within 30 days after surgery will be compared between the two study groups using the one-sided group sequential test of two proportions at the 2.5% significance level with a total of two looks at the data. The primary endpoint analysis will be performed on the ITT set. Since the ITT set includes all patients who were treated in the study regardless of any further medical or surgical treatments, it is expected, that the SSI rates 30 days post-surgery will be available for most patients. Nevertheless, it is possible that some patients do not reach the primary endpoint due to death, withdrawal of informed consent, loss to follow-up, or other unforeseen reasons. Patients who die before day 30 will be considered as having SSI at time of death regardless of the intervention group, unless SSI was documented earlier. All other missing primary endpoint data will be dealt with using multiple imputations based on binary logistic regression models including LOC, ASA, BMI, age, diabetes, type of surgery, duration of surgery, use of wound-edge protectors, and intraoperative changing of gloves.

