## Assignment of interventions: blinding

### Who will be blinded {17a}

The blinding procedure is restricted to participating patients, the statistician who performs the final analysis and the outcome assessors. Blinding of the surgical team that performs the intervention is impossible because of the distinctive smell of NaOCl/HOCl solution. Postoperatively, an outcome assessor of the local study group, who is unaware of the patient’s intraoperative intervention, will clinically assess the primary endpoint (SSI) on 3 postoperative study visits.

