### Methods for additional analyses (e.g. subgroup analyses) {20b}

Since randomization will be stratified by LOC, supportive analysis of the primary endpoint will be performed using a binary logistic regression model with dependent variable SSI and covariates intervention group and LOC. In addition, the following parameters might influence the outcome, which is why they will be included as model covariates in an additional model:Operation-related risk factors: (a) type of surgery; (b) duration of surgery; (c) NNIS Risk Score, (d) use of wound-edge protectors; (e) intraoperative changing of gloves before skin closure; (f) presence of an enterostomy; (g) administration and timing of antibiotic prophylaxis;Patient-related risk factors: (g) BMI; (h) ASA score; (i) Age; (j) diabetes; (k) smoking; (l) alcohol abuse; (m) Charlson Comorbidity Index, (n) history of SSI; (o) history of radiotherapy; (p) history of chemotherapy, (q) days of hospitalization prior to surgery.

Supportive analysis of the primary endpoint will be performed on the ITT set using multiple imputations for any missing SSI values and on the PP set. Secondary endpoints will be analysed by intervention arm on the ITT set, using appropriate descriptive statistics. Any explorative statistical testing will be performed using a significance level of 5%. The assessment of safety will be based on the frequency of AE/SAE as defined in the protocol within the safety population consisting of all patients randomized into the study.

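### The set called ITT is defined by receipt of irrigation after randomisation, not by randomisation, and the safety set has two definitions that cannot both be followed

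*Protocol article*

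**What the plan says.** All references are to the protocol article.

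- **Primary population.** Section {20a}, Statistical methods for primary and secondary outcomes: "The intention-to-treat (ITT) set consists of all patients who received irrigation of the abdominal cavity before closure of the abdominal fascia". The sentence goes on to require one of the study solutions. The section then says "Analysis will be performed as randomized regardless of the actual intervention and regardless of any further medical or surgical treatments", and "All primary and secondary analyses will be performed on the ITT set".
- **Safety population, first definition.** Same section: "The Safety (SA) set will consist of all patients in the ITT set, analysed as treated".
- **Safety population, second definition.** Section {20b}, Methods for additional analyses, assesses safety "within the safety population consisting of all patients randomized into the study".
- **Order of events.** Under Intervention description {11a} and Sequence generation {16a}, randomisation takes place at the end of surgery, before the fascia is closed. Under Concealment mechanism {16b}, the surgical team is told the result. Under Study setting {9}, the leading surgeon carries out the irrigation. Section {17a}: "Blinding of the surgical team that performs the intervention is impossible".
- **Patients who are not irrigated.** Section {11b} foresees patients without irrigation of the peritoneal cavity or wound and says "this does not automatically lead to exclusion of the study". It also lets excluded patients be replaced.
- **Mandatory exclusions after randomisation.** Sections {11d} and {18a} (Visit 2) require exclusion when postoperative intraabdominal irrigation is given through an irrigation-suction drain. Section {18a} also requires it when the wound is left incompletely closed or another wound procedure follows the study intervention.

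**The concern.** An intention-to-treat comparison is protected because membership is fixed at randomisation. Here it is fixed one step later, by whether the abdomen was irrigated with a study solution, and the person who irrigates knows the arm. If non-irrigation depended on both the arm and the patient's infection risk, the two groups in the primary test would no longer be comparable, and readers would not be warned because the set carries the ITT label. The only other set planned for the primary endpoint, the per-protocol set, is narrower still, so no all-randomised analysis is stated anywhere.

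The safety conflict needs no assumption about bias: the two sections give different denominators for the same adverse-event frequencies.

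**Working it through.** **1. Who is in which set**

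| Randomised patient | ITT set {20a} | Safety set {20a} | Safety set {20b} |
|---|---|---|---|
| Abdomen irrigated with assigned solution | in, assigned arm | in | in |
| Abdomen irrigated with the other study solution | in, assigned arm | in, as treated | in |
| Abdomen irrigated, wound rinse missed | in, assigned arm | in | in |
| Abdomen irrigated only with a non-study fluid | out | out | in |
| Abdomen not irrigated | out | out | in |

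The as-randomised rule settles the arm for patients already in the set; it does not bring in the last two rows. Those two rows are also exactly where the safety definitions differ.

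**2. The plan's own figures**

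Inputs from Sample size {14}: SSI 16% against 4%, one-sided 2.5%, 80% power, two looks, O'Brien-Fleming spending, continuity correction.

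- Efficacy bounds recompute to 2.963 and 1.969, as stated.
- Unpooled variance, a group-sequential inflation factor of 1.056 and the continuity correction give 115.5, so 116 per arm and 232 in total.
- Drop-out: 232 / (1 − 0.20) = 290.

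None of these depends on the set definition.

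**3. How much selective omission could matter (illustration)**

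The article gives no non-irrigation rate, so the following are assumptions: no true effect; 145 per arm; a common SSI rate p of 10% or 16%; a share q of the experimental arm dropped, with a 40% SSI risk; no drops in the control arm. The SSI rate among the experimental patients who remain is

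(p − 0.40q) / (1 − q).

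Example: p = 10%, q = 5% gives (0.10 − 0.02) / 0.95 = 8.4%, against 10% in the control arm.

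The one-sided error below is for a pooled z-test at the final bound 1.969, as a single look, from exact binomial probabilities averaged over the number dropped.

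| Share dropped | p = 10%: remaining rate | error | p = 16%: remaining rate | error |
|---|---|---|---|---|
| none | 10.0% | 2.5% | 16.0% | 2.4% |
| 2% | 9.4% | 3.6% | 15.5% | 3.2% |
| 3% | 9.1% | 4.4% | 15.3% | 3.6% |
| 5% | 8.4% | 6.5% | 14.7% | 4.7% |

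**4. The same check under other assumptions**

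- Omission in the experimental arm unrelated to risk: 2.4–2.5% throughout.
- Same share and same risk dropped in both arms: 2.3–2.5%.
- Selective omission as in step 3, but with a continuity-corrected test: 2.2%, 2.7%, 4.1% at p = 10% and 2.2%, 2.5%, 3.2% at p = 16%. Section {14} says the sample size calculation is continuity corrected; it does not say whether the final test is.

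**5. What an all-randomised set would cost in power**

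Suppose a share e of the experimental arm is not irrigated, is kept, and has the control risk. The experimental rate becomes 0.04(1 − e) + 0.16e. With 116 per arm (fixed design, no continuity correction) power is 86.6% at e = 0. It becomes 84.8%, 81.9% and 76.5% at e = 2%, 5% and 10% (rates 4.24%, 4.6%, 5.2%).

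**The case against.** The strongest reply is that little can go wrong in practice. Randomisation comes immediately before irrigation, irrigation is routine in both arms, and the most obvious deviation by an unblinded team, using the other arm's solution, leaves the patient in the set and in the assigned arm. The article gives no reason to expect non-irrigation to depend on arm and risk together. This stands, and it limits the point in three ways.

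- A reader might infer that the surgeon decides in general who is analysed. The text supports this only for patients whose abdomen is irrigated with neither study solution.
- A reader might infer that {20a} overrides {11b}. Section {11b} concerns exclusion from the study, covers the wound as well as the cavity, and says only that exclusion is not automatic. A patient can stay in follow-up and still fall outside an analysis set. The two sections sit uneasily together for patients without cavity irrigation, but they are not in flat contradiction.
- A reader might infer that the type I error is inflated. That requires omissions that are both high-risk and concentrated in the experimental arm; otherwise it stays near the nominal level.

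The reply does not rescue the label or the safety set. A set conditioned on treatment received is a modified ITT set however few patients it loses, and two incompatible safety definitions remain incompatible. Nor is this a detail left to a fuller document: the article states the definitions itself.

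**Conclusion.** The point holds in two parts. First, the primary population is a receipt-based set labelled ITT, and entry is settled after randomisation by people who know the arm. It affects only randomised patients who get no abdominal irrigation or only a non-study fluid. Second, the safety set is defined once as the irrigated patients and once as "safety population consisting of all patients randomized into the study"; the two sections must be reconciled.

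The size of any bias is unknown and may be nil. Under the stated assumptions (2–5% dropped from the experimental arm only, 40% SSI risk in those dropped, 145 per arm, no continuity correction in the test) the one-sided error is about 3.6–6.5% at a 10% SSI rate and 3.2–4.7% at 16%. It is about 2.5% if omission is unrelated to risk or equal in both arms. These figures show sensitivity; they do not predict what will happen in this trial, and the documents do not support saying that the primary test is biased. The case for change rests on the definitions, which are wrong as written and cheap to correct.

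**What to change.** 1. In {20a}, define the ITT set as all randomised patients, analysed in the assigned arm whether or not they were irrigated.
2. Name the irrigated subset modified ITT and use it for sensitivity analysis only.
3. State that exclusions and replacements after randomisation ({11b}, {11d}, {18a}) do not remove a patient from the ITT set, as far as consent allows. Without this clause the new definition could still be undone by those routes.
4. Use one safety definition in {20a} and {20b}: all randomised patients, grouped by the solution actually received, with non-irrigated patients listed separately.

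The cost is a few sentences, best settled before any unblinded look at the data, and follow-up of patients who would otherwise be dropped. The effect is slightly diluted if a few non-irrigated patients are kept: about 2 percentage points of power at 2% non-irrigated (86.6% to 84.8%) and about 5 at 5% (86.6% to 81.9%), in the simplified calculation above. The sample sizes of 232 and 290 do not change.
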